### 3.3 Study design

This study is an open-label, multicentric, international two-arm, randomized controlled trial.

The downside of the selected design (RCT) will be the study duration (i.e., three years). The randomization will permit to minimize biases by having two comparable groups.

### 3.4. Study intervention

After PD, patients will be randomized to receive either EEN or oral nutrition. Patients included in the EEN arm will receive, in addition to oral nutrition based on the current care maps, enteral nutrition according to the following scheme that was established in accordance with nutritionists:

- Six hours after the operation, a low flow enteral feeding will be initiated (21 ml/h, 250 ml/12h), and based on a Isosource® Energy Fibre solution (hypercaloric, 400 kcal).
- If the tolerance is subjectively good, with a visual analogue scale  $\leq 4/10$ , the flow will be increased on first postoperative day (POD), at the flow of 42 ml/h (500 ml/12h, 800 kcal).
- On POD 2: increased flow to 62.5 ml/h (750 ml/12h, 1200 kcal)
- On POD 3: increased flow to 83.5 ml/h (1000 ml/12h, 1600 kcal)

If the tolerance is not satisfactory ( $>4/10$ ), the current flow will be maintained 24 hours more, decreased or put on hold for a couple of hours (depending on the symptoms of the patient), and increased the next day if tolerated until the maximum of 1000 ml/12h.

The diet will be infused over 12 hours with a pump and controlled flow rate. EEN will be continued

until oral food intake will have reached more than 50% of nutritional requirements. Daily nutritional requirements will be defined as 30 kcal/kg if BMI <30 kg/m^2 and 25 kcal/kg if BMI ≥30 kg/m^2 (protein target: 1.5 g/kg/day). The oral intake will be assessed by the dietitian.

If a patient in the EEN group loses or displaces its nasojejunal tube (vomiting, accidental removal), a new probe will be replaced under endoscopic control by the gastroenterologist. If that happens a second time, another attempt to put the nasojejunal tube will not be made (the patient will remain in the study). In the same previous scenario (nasojejunal tube expulsion), and if the patient suffers from DGE, a nasogastric tube will be installed at the same time. If the patient suffers from DGE and the nasojejunal tube is in place, a nasogastric suction tube will be installed in addition, and enteral feeding will be continued. Parenteral nutrition will be used to complete the missing caloric needs. In the control group (without nasojejunal tube), in case of DGE, a nasogastric suction tube will be installed (the patient will remain in the study).

The use of parenteral feeding will be standardized similarly in both groups. A parenteral nutrition will be initiated if the caloric intake is <50% of caloric requirements for 24 hours and from POD 3. Parenteral nutrition will be continued until the total caloric intake without the parenteral nutrition reach >50% of daily caloric needs and until no more nasogastric tube will be in place.

Note that according to the current standard care, endoscopies are also performed in case of repeated vomiting, DGE, loss of feeding tube or to put a triluminal probe. No additional endoscopies will be performed as study procedures.

## **4 STUDY POPULATION AND STUDY PROCEDURES**

### **4.1 Inclusion and exclusion criteria, justification of study population**

Participants fulfilling all of the following inclusion criteria are eligible for the study:

- Patient scheduled for elective open PD.
- Patient ≥18 years old.
- Patient at nutritional risk, i.e., with NRS ≥3.
- Signed informed consent

The presence of any one of the following exclusion criteria will lead to exclusion of the participant:

- Patient not able to give informed consent as documented by signature of consent form (e.g., vulnerable patients).
- Enteral feeding already initiated preoperatively.
- Language barrier.
- Inability to follow the procedures of the study, e.g., due to language problems, psychological disorders (i.e., eating disorders and bipolar disorders), or dementia.

The total number of included patients will be 144 (72 in each group, see section 5.0 for further details). The choice of the patient population is justified by the fact the patients undergoing PD often are malnourished (cachexia due to cancer or chronic pancreatitis) and are at nutritional risk postoperatively due to the important stress response induced by this major abdominal surgery. As malnutrition is a risk factor for complications, EEN might reduce the morbidity burden after PD.

#### **4.2 Recruitment, screening and informed consent procedure**

The study will be proposed to any patient planned for a PD meeting inclusion criteria. Of note, patients are usually referred to our consultation by external physicians or hospitals. The study will be presented to the patients during the first preoperative consultation by the investigators at the hospital. Expected benefits (fewer postoperative complications) and potential disadvantages as well as risks (poor tolerance of the nasojejunal tube, nausea, vomiting, diarrhea, tube obstruction, bronchial inhalation) will be explained. An information sheet will be given to the patient during the preoperative consultation. The patient will have the opportunity to ask questions.

A time of reflection will be given (at least 24 hours). The consent form will therefore be obtained at last the day before the intervention.

The investigators will explain to each participant the nature of the study, its purpose, the procedures involved, the expected duration, the potential risks and benefits and any discomfort it may entail. Each participant will be informed that the participation in the study is voluntary and that he or she may withdraw from the study at any time and that withdrawal of consent will not affect his or her subsequent medical assistance and treatment.

The participant will be informed that his or her medical records may be examined by authorized individuals other than their treating physician.

All participants for the study will be provided a participant information sheet and a consent form describing the study and providing sufficient information for participant to make an informed decision about their participation in the study.

The formal consent of a participant, using the approved consent form, will be obtained before the participant is submitted to any study procedure.

The consent form will be signed and dated by the investigator or his designee at the same time as the participant signs. A copy of the signed informed consent will be given to the study participant. The consent form will be retained as part of the study records. The informed consent process will be documented in the patient file and any discrepancy to the process described in this protocol will be explained.

#### **4.3 Study procedures**

Given the rate of annual procedures, a recruitment of about 60% of eligible patients, and based NUTRIWHI Trial  
Version 5.0, 20/10/2023

[figure not shown]

on the experience of two randomized studies successfully completed in the Visceral Surgery Department (NCT0508300, NCT00512213), the planned overall study duration is three years including the recruitment period and follow-up. For patients the study duration will be from enrolment until POD 90, date of last follow-up phone call. The expected hospitalization duration for each patient will be approximately 14 days, which is the current mean hospital stay after PD in our department.

Eligibility of the patients will be confirmed on the day before the operation (day -1). Then, patients will be randomized before the operation (day -1) in either the control arm or the experimental one (EEN).

Standardized surgical procedure in all eligible patients: In terms of surgical details, all patients will receive a prophylactic dose of antibiotics (cefuroxime) 30 minutes before incision and first have exploratory laparotomy followed by conventional or pylorus-preserving PD. Pancreaticojejunostomy will be performed. End-to-side hepaticojejunostomy will be performed with single-layer interrupted sutures. A gastrojejunostomy will finally be constructed. Two perianastomotic drains will be placed.

Specific study procedure: At the end of surgery (after the three anastomoses are finished but before closure of the abdomen) and in the EEN study group only, a polyurethane single or double lumen feeding nasojejunal tube (Freka®) 8F will be inserted by the anesthesiologist and placed under direct palpation and visual control by the surgeon, 30 cm distally to the gastrojejunostomy into the jejunum. The tube will be attached according to current practice to the nose wing with a tape. The patient will therefore be under general anesthesia during tube insertion and no x-ray control will be needed.

Postoperatively, patients will receive standardized perioperative care according to the ERAS protocol in both arms.

From a nutritional point of view, this includes:

- The day before surgery: 2 carbohydrate drinks of 200 ml
- The operative day: 2 carbohydrate drinks of 200 ml up to 2 hours preoperatively, then postoperative free drinks
- On postoperative day (POD) 1: bouillons, creams, yogurts, drinks  $\geq 2l$
- On POD 2: light diet, drinks  $\geq 2l$
- On POD 3: normal diet (half portion)
- On POD 4: normal diet (full portion)

From POD 1, patients of both groups will receive two oral nutritional supplements (Resource® Ultra XS 125 ml, 280 kcal, 18 grams of proteins or analogous products) until discharge. In terms of intravenous infusions, a parenteral crystalloid solution will be used (Ringer-Lactate): 1000 ml during operative day and on POD 1, 500 ml during POD 2 and 3, then 250 ml, if necessary, NUTRIWHI Trial

until POD 8 (minimum for maintenance of the central venous line). Anti-nausea agents (ondansetron 4 mg 3x/j and mephameson 4 mg 1x/j) as well as laxatives (magnesium hydroxyde 4.5 g 2x/j) will be used daily for 3 days, then on demand. Prokinetic agent (metoclopramide 10 mg 3x/j) will be used on demand. An anti-acid (esomeprazole 40 mg 1x/j) will be introduced for the duration of the hospitalization. Digestive enzymes will be prescribed from the first postoperative day (Creon 40'000 UI 3x/j).

In terms of mobilization, patients will be stimulated by nurses/physiotherapists according to the following plan:

- Operative day: just get up from bed
- On POD 1: walk once during the day, spend  $\geq 6$ h out of bed (3 x 2h)
- On POD 2 to discharge: walk twice during the day, spend  $\geq 8$ h out of bed (4 x 2h)

In our current practice, no suction gastric tube is left in place after the operation.

A standard nutrition protocol for the EEN intervention group will be prescribed as established in accordance with the nutritionists (see "3.4 Study intervention" for details). For patients randomized into the oral nutrition group they will receive the current postoperative management and receive from POD 1 an oral nutrition that will be gradually increased if tolerated until a normal diet (see above).

Several blood tests will be performed during the postoperative period. A timeline summary table of all study visits, relevant procedures, and samplings is shown in Appendix 1 (schedule of assessments).

Demographic disparities or difference in patient characteristics could be a source of bias. To reduce this risk, we decided to undertake a randomization of the participants. Moreover, heterogeneity in general management between centers might be a source of bias. Randomization will be stratified by center to decrease the risk of center bias.

#### **4.4 Withdrawal and discontinuation**

Patients will be withdrawn from the study if they leave the operation room with only a suction nasogastric tube in place or in case of withdrawal of informed consent, non-compliance to the study protocol, or due to safety concerns. Participants will not be replaced and considered as dropouts. Study data already collected on a participant until the time of withdrawal will still be used for analysis in a coded manner. No further data will be collected however from that time onwards.

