## **5 STATISTICS AND METHODOLOGY**

### **5.1. Statistical analysis plan and sample size calculation**

A statistician was involved in the study design and estimate of the sample size.

Null hypothesis  $H_0$ : EEN has no effect on postoperative complications (CCI) in the population (and therefore the observed effect is entirely due to chance):  $p_2 = p_1$

Scientific hypothesis  $H_1$ : EEN has an effect on postoperative morbidity (CCI) in the population (and therefore the observed effect is not entirely due to chance):  $p_2 > p_1$

According to a previous randomized trial including a series of PD and assessing a realimentation process (enteral vs. parenteral), the mean CCI was impacted of about 30% (32.8 vs. 24.2). Another study reported a mean CCI of 38 after PD.

Based on the above results, we hypothesize that EEN will reduce by 30% a mean CCI of 35 (+/- 20) of the oral nutrition group. We will therefore expect a mean CCI for the treatment group (EEN) of 24.5 (SD 20). In this superiority study, for a power of 80% and a significance level of p-value  $\leq 0.05$  (two-sided alpha), we will therefore need 57 patients per group according to the sample size calculation. Nevertheless, we will increase the sample size to a total of 144 patients to take into account 20% of drop-outs (e.g., due to non realization of pancreatoduodenectomy or consent withdraw) at 90 days (primary endpoint evaluation). We will therefore need to enroll 72 patients per group in the trial.

The study will be closed once the required 144 patients will be included. No interim analysis will be performed.

Normality of distribution will be determined by the Kolmogorov-Smirnov test and quantile-quantile plots of dependent variables for all continuous variables.

We will use a Student *t*-test to evaluate if the primary outcome (CCI) can significantly be reduced by EEN compared to the control group (comparison of mean CCI hypothesizing a normal distribution). For the analysis of all secondary endpoints, we will also use *t*-tests or chi-squared tests based on the variable types. Regarding the questionnaires filled 4 times during the study, tests specific to repetitive ordinal measures will be used.

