The analysis will be based on the intention-to-treat method and not per protocol. We will perform an intention-to-treat analysis so that all patients being intended to treat will be analyzed in the statistics independently. All patients will therefore be analyzed according to the group in which they were initially randomized.

Blocked randomization will be done using a computerized algorithm via REDCap by a research coordinator (different from the person who included the patient) the day before surgery. The proportion of "study" (EEN) and "control" (oral nutrition) subjects will be 1:1 (mix of variable block sizes of 4, 6, and 8 patients, randomly selected). Before surgery, only the responsible surgeon will know the allocation group. Postoperatively, the inclusion in the different groups will be known by the caregiver team and the patient, as it is not possible to blind the intervention (nasojejunal tube).

The investigators, the outcome adjudicators, and the data analysts will be blinded (allocation concealment).

The statistical package used for analysis will be SPSS version 26 (IBM Corp., Armonk, NY, USA).

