### **Follow up of (Serious) Adverse Events**

Participants who experience adverse events will be retained in the study. A follow-up of SAE will be organized accordingly, under the supervision of the sponsor, depending on the type of event. Patients with SAE will be followed until resolution or stabilization of the effect will be noted.

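### Section 4.4 ends outcome collection for patients withdrawn over tube status, non-compliance or safety, so the as-randomised analysis of 90-day CCI promised in section 5.1 cannot be complete, and the tube rule acts unequally by arm

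*Protocol*

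**What the plan says.** Protocol section 4.3 places randomisation on day -1, before the operation. Section 4.4 then lists grounds for withdrawal that can only arise later. The first is "Patients will be withdrawn from the study if they leave the operation room with only a suction nasogastric tube in place". Apart from withdrawal of consent, the others are "non-compliance to the study protocol, or due to safety concerns". On the status of these patients it says "Participants will not be replaced and considered as dropouts". Data gathered up to withdrawal are kept and used, but "No further data will be collected however from that time onwards".

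Section 5.1 commits to intention to treat rather than per protocol: "All patients will therefore be analyzed according to the group in which they were initially randomized". Section 3.2 defines the primary endpoint as CCI within 90 postoperative days, and Appendix 1 schedules its first assessment at discharge. Section 5.2 mentions multiple imputation only for variables that are not endpoints.

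Other sections keep patients in. Section 3.4 retains an EEN patient after a second loss of the nasojejunal tube, and a control patient who receives a suction tube for delayed gastric emptying. Section 6.2 says: "Participants who experience adverse events will be retained in the study".

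**The concern.** Withdrawal here means leaving the study, not merely stopping the study feeding. A patient withdrawn on leaving theatre contributes no CCI. One withdrawn later contributes an index cut off before day 90, and because CCI accumulates complications, a truncated value can only equal or understate the full one. No analysis plan can recover outcomes that nobody collected; it can only model them under assumptions the data cannot test.

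One withdrawal ground also depends on the arm by construction, because only EEN patients are given a nasojejunal tube. What is at stake is the protection that randomisation gives to the primary comparison. The result could be reported as intention to treat although part of the randomised set was lost for reasons tied to allocation or to the postoperative course.

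**Working it through.** **1. The plan's own figure.** Inputs from section 5.1: means 35 and 24.5 (difference 10.5), SD 20, two-sided alpha 5%, power 80%, drop-out 20%.

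- n per arm = 2 × (1.96 + 0.842)² × 20² / 10.5² = 56.95, rounded up to 57.
- 57 / 0.80 = 71.25, rounded up to 72 per arm, 144 in total.

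Both figures reproduce, so the fault is not arithmetic. The plan is powered on 57 of 72 per arm, which leaves room for 72 − 57 = 15 patients per arm without a day-90 outcome, for any reason.

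**2. The tube rule by arm.** Section 4.3 places a nasojejunal tube in the EEN group only. For a patient who leaves theatre with a suction tube:

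| Arm | Nasojejunal tube | Result under 4.4 |
|---|---|---|
| Control | never | withdrawn |
| EEN | placed | stays in |
| EEN | not placed | withdrawn |

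The rule is therefore not confined to controls, but the same need for suction leads to different outcomes by arm. Section 5.1 adds that the responsible surgeon knows the allocation before surgery.

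**3. Retention rules side by side.**

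| Event | Section 4.4 | Elsewhere |
|---|---|---|
| Suction tube only, on leaving theatre | withdrawn | control with a later suction tube for delayed gastric emptying stays (3.4) |
| Non-compliance, undefined | withdrawn | EEN patient stays after second tube loss (3.4) |
| Safety concerns | withdrawn | patients with adverse events stay (6.2) |

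**4. What a bias would do (illustration).** The protocol gives no withdrawal rates and no CCI for such patients, so every bias value below is an assumption.

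- Standard error = 20 × √(2/57) = 3.75.
- Type I error = P(|Z + bias/SE| > 1.96). A net bias of 2 points gives 2/3.75 = 0.53, and the error is 8.3% instead of 5%.
- Shift of an arm mean = share removed × excess CCI of those removed over those who remain. Losing 10% of controls with an excess of 20 points lowers the control mean by 0.10 × 20 = 2.0. Losing 15% of the EEN arm with an excess of 15 points lowers the EEN mean by 0.15 × 15 = 2.25.
- If both happened, the net is 2.25 − 2.0 = 0.25 points, and the type I error stays at about 5%.

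Losing high-CCI patients from the EEN arm favours EEN; losing them from the control arm works against it.

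**5. Power if everyone is followed.** With 72 per arm, SE = 20 × √(2/72) = 3.33. Suppose a share d of EEN patients is analysed without having had any benefit; the expected difference is then 10.5 × (1 − d).

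| d | Difference | Power, 72 per arm |
|---|---|---|
| 0 | 10.50 | 88.3% |
| 5% | 9.98 | 84.9% |
| 10% | 9.45 | 80.9% |
| 15% | 8.93 | 76.3% |
| 20% | 8.40 | 71.2% |

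**The case against.** Several things can fairly be said for the plan.

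- Data up to withdrawal are kept, and an as-randomised analysis under stated missing-data assumptions remains possible. Its handling of a missing CCI may be set out in a statistical analysis plan that is not shown. A reader might infer that intention to treat is impossible altogether; the protocol does not support that. What stands is that a complete as-randomised analysis is out of reach for the withdrawn patients.
- The tube trigger applies only on leaving theatre, and section 4.3 says no suction gastric tube is left in place in current practice. It may be rare. The asymmetry stands; its frequency is unknown.
- A reader might infer that non-compliance chiefly removes EEN patients who cannot tolerate the tube. Section 3.4 handles intolerance and repeated tube loss within the protocol, and section 4.4 leaves non-compliance undefined for both arms.
- A reader might also infer that the withdrawn patients are the sicker ones. Nothing in the document shows this. The drop-out allowance in section 5.1 names only other examples: "20% of drop-outs (e.g., due to non realization of pancreatoduodenectomy or consent withdraw) at 90 days (primary endpoint evaluation".
- Retaining patients with adverse events can coexist with exceptional withdrawal for safety, and section 6.2 follows serious events until they resolve or stabilise. This is an ambiguity to settle rather than a flat contradiction.
- Ending collection when consent is withdrawn is ordinary practice and is not criticised here.

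**Conclusion.** The point holds as a conflict between a fixed conduct rule and the stated analysis principle. It rests on the protocol's text alone: randomisation on day -1, withdrawal from the study after that, no later data, an endpoint running to day 90, and a promise to analyse everyone as randomised. That the tube rule acts unequally by arm follows from its wording.

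The size of the consequence is not established. The number of patients affected, their CCI and the direction of any net bias cannot be derived from the document. The 8% type I error is conditional on an assumed 2-point net bias, and losses in both arms could largely offset each other. The matter should still be settled by amendment, because it concerns the primary endpoint and outcomes not collected may not be recoverable later.

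**What to change.** Amend section 4.4 to distinguish stopping the study intervention from leaving the study. Tube status on leaving theatre, non-compliance and discontinuation for safety should not end outcome collection. CCI, Clavien grade and readmissions are collected to day 90 for these patients, who are analysed in the arm to which they were randomised. Only withdrawal of consent to further data collection ends it.

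Reconcile sections 3.4, 4.4, 5.1 and 6.2 so that sites have one retention rule. Which tube and safety rules apply clinically is for the sponsor to decide. Whether patients whose pancreatoduodenectomy is not carried out belong in the primary analysis is a separate question about the estimand: section 4.4 does not list them, and this amendment need not settle it.

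The cost is amendment wording and a little more follow-up through the existing visits, medical records and the day-90 call. The statistical price is some dilution of the effect. If all 72 per arm are followed, the planned 144 patients keep about 80% power up to roughly 10% dilution; at 15% dilution power falls to 76%.
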